**Methods:**

Thirty adults (over 18 years of age) with post-traumatic GON will be randomized into one of three groups: (1) autologous PRP injection, (2) steroid/anesthetic injection (standard care), or (3) placebo injection with normal saline. Injections will be performed to the greater occipital nerve under ultrasound guidance by a trained physician. Daily headache intensity and frequency data will be collected pre-injection and for the duration of the study period. Feasibility will be defined as greater than 30% recruitment, 70% completion of intervention, 70% retention, and less than 2 minor adverse events. Exploratory outcomes will be explored using the Headache Impact Test-6 (HIT-6, a valid and reliable 6-item questionnaire for assessment of the impact of headaches across different diagnostic groups of headaches) and the quality of life in following brain injury questionnaire (QOILIBRI).

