Multiple animal and in vitro studies have demonstrated PRP’s ability to assist in remyelination, axonal regeneration, and functional neurologic recovery in models of peripheral nerve injury [20, 23–32]. There have been few in vivo studies of PRP in treatment of peripheral neuropathies with variable success rates [33–37]. One randomized controlled trial found significant pain reductions in 60 patients with carpal tunnel syndrome and improvement of multiple markers of nerve function which persisted to 6 months following a single PRP injection [20]. Another clinical trial found significant improvement in pain following perineural PRP injections in patients with diabetic polyneuropathy [30].

These findings are encouraging as they reveal new therapeutic avenues in the management of peripheral nerve disorders. To our knowledge, PRP has not been investigated as a treatment for GON. We believe that PRP’s physiology, demonstrated efficacy, and safety profile make it an exciting and novel strategy to treat this debilitating condition. This study will investigate the feasibility of a randomized control pilot study for the treatment of GON in patients with post-traumatic headache using PRP. This pilot trial will evaluate the ability to recruit patients, retain patients throughout the protocol and the feasibility of implementing randomization using PRP for the treatment of patients suffering with GON following TBI. Our specific objectives are the following:
Evaluate the feasibility of a randomized pilot study of PRP as a treatment for patients with GON and post-traumatic headache in terms of recruitment (greater than 30%), attendance (70% intervention appointment attendance), retention (greater than 70% complete protocol), and acceptability of the protocol.Evaluate the safety profile of PRP for the treatment of GON in patients with post-traumatic headaches with less than 2 minimal adverse events.Exploratory objectives include evaluating whether patients with GON and post-traumatic headaches receiving PRP have significantly decreases pain, improved function, and quality of life, compared to patients receiving cortisone/anesthetic and normal saline injections.

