### Measures

Demographic information will be collected 2 weeks prior to starting the study including age, sex, weight/height, education, family history, past medical history, and medication use. Headache history will be collected including headache frequency, severity, as needed medication-use, type of headache, associated symptoms (i.e., paresthesia, fronto-orbital pain, nausea, vomiting), and headache triggers.

Questionnaires will be completed 2 weeks prior to injections, 1 week, 1 month, and 3 months post-injection. A daily headache diary provided via mobile application (Secure RedCap) available in iPhone or android device will be provided to record daily records of NPRS, headache frequency, and medication-use. Patients will complete daily headache diaries beginning at 2 weeks pre-injection and ending 3 months post-injection. See Figure 1 for a schematic of the study design.

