### Primary outcomes

The primary outcomes of this trial will assess the feasibility of a double-blinded randomized control trial for the treatment of GON in patients with post-traumatic headaches. This pilot trial is a smaller version and will aim to inform a more extensive and larger version of this randomized control trial. Specific outcomes for evaluation will include the following:
Recruitment: Ability to recruit at least 30% of those patients screened for participation.Intervention attendance: At least 70% of those patients recruited for the study will attend and participate in the primary intervention.Retention: At least 70% of those receiving the primary intervention will complete the 3-month follow-up.Adverse events: Adverse events will be minimal. No more than 1 individual will have an adverse event. Any adverse event will be minor and reversible (i.e., nausea, light headedness, temporary pain at site of injection).

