### Attrition and adherence

Participants will be withdrawn from the study if there is a change in routine medications during the study period or if they do not complete study questionnaires. Daily headache diaries will be completed by all participants for the duration of the study submitted on their mobile device. In the event that daily diaries are not completed, reminders will be sent out by the study team.

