### Data analysis

The primary outcomes for this pilot trial require descriptive statistics for recruitment, completion of primary assessment, retention, and adverse effect profiles. For exploratory outcomes, change in NPRS, HIT-6, and QOLIBRI at 1 and 3 months following intervention for patients receiving PRP compared to steroid/anesthetic and normal saline will be analyzed. A two-way mixed ANOVA test will be completed to evaluate the change in NRPS between groups. Chi-square testing will be performed to determine the relationship between basic characteristics in the three groups. For secondary outcomes, Kruskal-Wallis non-parametric analysis based on ranks will be completed correcting for multiple comparisons with Bonferroni correction. All results will be presented with 95% confidence intervals. Results will be preliminary and should be interpreted with caution due to the small sample size.

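### Withdrawing participants for uncompleted questionnaires, with no stated threshold, mixes protocol-imposed removal into the primary retention outcome and may lose obtainable 3-month data

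*Protocol article*

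**What the plan says.** All references are to the protocol article.

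- **Attrition and adherence** gives two grounds for withdrawal in one sentence. The first is a medication change: "Participants will be withdrawn from the study if there is a change in routine medications during the study period". The second concerns forms: "or if they do not complete study questionnaires". No number of missed forms, visit or grace window is attached to the second.
- The same section treats missed diaries differently: "In the event that daily diaries are not completed, reminders will be sent out by the study team".
- **Measures** sets the schedule: "Questionnaires will be completed 2 weeks prior to injections, 1 week, 1 month, and 3 months post-injection". Three of the four occasions fall after injection. The daily diary, which records the NPRS, runs from 2 weeks before injection to 3 months after it.
- **Primary outcomes** defines retention: "At least 70% of those receiving the primary intervention will complete the 3-month follow-up". The objectives at the end of **Background** word it differently: "retention (greater than 70% complete protocol".
- **Data analysis** makes the feasibility outcomes descriptive: "The primary outcomes for this pilot trial require descriptive statistics for recruitment, completion of primary assessment, retention, and adverse effect profiles".

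Nothing in the article provides for continued follow-up of a withdrawn participant.

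**The concern.** Retention is a primary outcome of this pilot, and the Primary outcomes section says that the pilot is to inform a larger trial. The withdrawal rule acts directly on that outcome. A participant removed over a 1-week or 1-month questionnaire becomes a retention failure, whether or not that person would have come at 3 months. The reported figure then combines people who chose to leave with people whom the protocol removed, and a larger trial planned on it would inherit attrition that its own rules need not produce.

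Data are also at stake. The leading exploratory outcome is the NPRS at 3 months, and the NPRS is recorded in the diary. Withdrawal over a missed HIT-6 or quality-of-life form could therefore end collection of pain scores that the participant was still supplying. With 30 people in three arms, each such loss counts. An analysis plan could not repair this afterwards, because the data would not have been collected.

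**Working it through.** The plan has no dropout allowance or retention calculation to reproduce. What follows first traces the rule through the text and then illustrates its possible size.

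**Tracing the rule**

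1. Questionnaires are due at 1 week, 1 month and 3 months after injection (Measures).
2. Non-completion leads to withdrawal from the study (Attrition and adherence).
3. Retention requires completing the 3-month follow-up, among those injected (Primary outcomes).
4. Hence a withdrawal at 1 week or 1 month is a retention failure. A missed 3-month form leaves no later data to lose. A missed pre-injection form bears on attendance, because the retention denominator is those injected.

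**Inputs for the illustration**

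- From the plan: 30 participants (abstract: "Thirty adults (over 18 years of age) with post-traumatic GON will be randomized into one of three groups"); the 70% criterion, so 0.70 × 30 = 21 retained; three post-injection questionnaire visits.
- Assumed, not in the documents: all 30 are injected; each visit is completed with probability *p*, independently of the others; nobody leaves for any other reason.

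**Formulas for expected retention**

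- No withdrawal rule, only the 3-month visit counts: *p*.
- Strict trigger, one miss withdraws: *p*³.
- Lenient trigger, two misses withdraw: the 3-month visit must be completed and at most one of the two earlier visits missed, so *p* × [1 − (1 − *p*)²].

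The chance of meeting the criterion is the exact binomial P(X ≥ 21) with n = 30 and the relevant rate.

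| *p* | No rule: rate, chance | One miss: rate, chance | Two misses: rate, chance |
|---|---|---|---|
| 0.95 | 95.0%, >0.999 | 85.7%, 0.993 | 94.8%, >0.999 |
| 0.90 | 90.0%, 0.9995 | 72.9%, 0.72 | 89.1%, 0.999 |
| 0.88 | 88.0%, 0.998 | 68.1%, 0.50 | 86.7%, 0.996 |
| 0.85 | 85.0%, 0.990 | 61.4%, 0.22 | 83.1%, 0.98 |

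For example, at *p* = 0.90: 0.90³ = 0.729, and 0.90 × (1 − 0.10²) = 0.891.

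Under the strict trigger, expected retention falls below 70% once *p* is below 0.7^(1/3) = 0.888.

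**Adding voluntary dropout.** Let a share *s* be willing to stay to 3 months. With *s* = 0.90:

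- *p* = 0.90: 0.90 × 0.90 = 81.0% without the rule and 0.90 × 0.729 = 65.6% with the strict trigger. The chances are 0.95 and 0.38.
- *p* = 0.98: 88.2% and 84.7%. The chances are 0.998 and 0.989.

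**Correlation.** If the same people miss every visit (perfect positive correlation), retention is *p* with or without the rule and the gap vanishes. Partial positive correlation lies between that and the table.

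**The case against.** **The wording does not say one missed form.** It is plural and has no threshold, so persistent non-completion is an equally fair reading. A reader might infer that a single missed form always ends participation; the text does not establish that. This stands, and the strict column above is a bound, not the rule. It does not remove the point: at 85% completion the chance of passing is 0.22 or 0.98 depending on a trigger that the protocol never states.

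**Retention is not redefined as form completion.** A reader might infer that the figure measures completion of every form instead of willingness to stay. The documents do not support this. The outcome is completion of the 3-month follow-up, and failures would include voluntary dropout and medication-change withdrawals as well. The objective's wording about completing the protocol even suggests that some adherence to the schedule was meant to count. The defect is that different causes are mixed.

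**The numbers are assumed.** No completion rate appears in the documents, visits within a person are probably positively correlated, and at 95% or more the feasibility verdict hardly moves. All of this stands.

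**There are safeguards.** A research assistant periodically checks completeness (Data management and monitoring), and descriptive reporting allows reasons for withdrawal to be shown. Both help, but neither suspends the rule.

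**Loss of data is inferred.** The article does not say what happens to a withdrawn participant's diary, and a full protocol might. So it is right to say that data may be lost, not that they will be. That missed forms depend on symptoms is plausible, but the documents do not show it.

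**Conclusion.** The point holds in a limited form. The protocol contains an explicit rule, not merely a missing detail, that turns uncompleted questionnaires into withdrawal at an undefined threshold. Anyone removed under it before 3 months counts against a primary outcome that asks only about the 3-month follow-up. Retention will therefore combine voluntary and protocol-imposed loss, and 3-month data that could have been had may not be collected.

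The size cannot be fixed from the documents. With a one-miss trigger, independent visits, 30 injected and no other dropout, the rule could decide the feasibility verdict at 85% to 90% completion per visit, and matters little at 95% or above. With a two-miss trigger or strongly correlated visits, the effect is small throughout. No figure stated in the plan is wrong because of this. The change is worth making because it is cheap and the retention estimate feeds the design of the next trial.

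**What to change.** 1. In Attrition and adherence, delete the questionnaire ground for withdrawal, and only that. The medication-change ground in the same sentence lies outside this change and is left as it is.
2. State in its place that a missed questionnaire is treated as missing data, prompts the reminders already used for diaries, and does not end participation; all later questionnaires and diaries are still requested.
3. In Primary outcomes, count as retained those injected participants who provide 3-month data, whatever was missed earlier.
4. Report separately, as descriptive feasibility results, questionnaire completion at 1 week, 1 month and 3 months, and the number of any protocol-imposed withdrawals with their reason.

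**Cost.** This needs a wording amendment, for which the article describes a route through the ethics board, and reminders for questionnaires as well as diaries. It needs no added visits or participants. Recruitment was under way at submission, so anyone already withdrawn on this ground should be reported as such. The downside is that some intermittently missing 1-week and 1-month values will stay in the data set and the exploratory analysis must accommodate them.

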### Data management and monitoring

Participants will be assigned a study ID at the time of study enrolment. All identifying information will be removed once study participant numbers have been assigned and data is collected. Study data will be entered into a highly secure electronic REDCap database (REDCap 7.6.9 2020 @ Vanderbilt University). Only research team members will have access to this database. Paper copies of any data or participant information will be stored in a secure fashion. All data will be retained for 5 years following project completion in accordance with the University of Calgary Conjoint Health Research Ethics Board.

There will not be a formal data monitoring committee; a research assistant will periodically evaluate participant data for completeness and inform investigators of any issues. Adverse events will be reported via telephone or email, a research assistant will contact participants for further details at the time of reporting. A study physician will be alerted of any serious adverse events that require immediate attention.

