### Blinding and randomization

Each participant will be randomized following screening and enrollment in the study. Participants will be randomized (via sealed envelope) by a blinded research assistant in a 1:1 fashion to one of three treatment arms: (1) autologous PRP injection, (2) steroid/anesthetic injection (standard care), or (3) placebo injection with normal saline. All patients will undergo 60 mL blood draw on their scheduled day of injection. Whole blood samples will be prepared in the PRP group only; otherwise, they will be discarded appropriately. Syringes (3 mL each) will be prepared by a research assistant and will be covered in an opaque tape so the physician providing the injection is blinded to the type of injectate. The physician will fill out a questionnaire at the time of injection indicating their best guess of the syringe contents, which will be evaluated afterwards, to ensure adequate blinding. Unblinding will occur only in extraordinary circumstances if knowledge of the actual treatment received is deemed essential to providing further patient care.

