### Interventions

Injections will be prepared as stated below. Patients will be asked to complete a numeric pain rating scale (NPRS) immediately pre- and post-injection. Patients will be asked to refrain from use of anti-inflammatory medications for 2 weeks prior to the injection and for 2 weeks following the injection due to the possible inhibitory effect on the action of PRP. Two 3 mL syringes with 2 mL of injectate (PRP, steroid/anesthetic, or normal saline) will be prepared for each participant. Patients will be assessed at the time of injection and will receive a single injection, if experiencing unilateral symptoms only, or two injections to each greater occipital nerve, if symptoms are bilateral. Patients will be monitored for 30 min following injection for any immediate adverse reactions, such as local reaction, increased pain intensity, anaphylaxis, nausea, or dizziness.

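### After the 30-minute post-injection observation, the only adverse-event route described is a spontaneous telephone or email report, so later minor events can be missed and the limit of one affected person met for that reason

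*Protocol article*

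**What the plan says.** Adverse events are one of four primary outcomes. Under Primary outcomes the pass mark is "No more than 1 individual will have an adverse event", and any event is expected to be minor and reversible, such as nausea, light-headedness or passing soreness at the injection site. The abstract puts the limit as "less than 2 minor adverse events", which counts events and not people.

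Two sources of adverse-event data are described:

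- **On the day** (Interventions): "Patients will be monitored for 30 min following injection for any immediate adverse reactions, such as local reaction, increased pain intensity, anaphylaxis, nausea, or dizziness".
- **Afterwards** (Data management and monitoring): "Adverse events will be reported via telephone or email", and once a report arrives a research assistant gets in touch to obtain the details.

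The same section provides no data monitoring committee; a research assistant checks the data for completeness.

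The trial also has regular contact with participants. Under Measures, "Questionnaires will be completed 2 weeks prior to injections, 1 week, 1 month, and 3 months post-injection", and a daily diary runs to 3 months. The diary is described as covering pain score, headache frequency and medication use. The named questionnaires are the HIT-6 and the QOLIBRI. None of these is described as a source of adverse events.

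**The concern.** The safety criterion turns on whether the count stays at 0 or 1 or reaches 2. A single missed person can change the answer. In the procedure as described, staff contact follows a report and does not prompt one, so from the end of the observation window until 3 months an event is counted only if someone decides to telephone or write. The events the plan expects are minor and self-limiting, and these are the ones a participant has least reason to report unprompted.

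The error runs in one direction. A missed event can only help the criterion to be met. A pass would not show whether there were few events or few reports, and a larger trial planned from this pilot could start from an event rate that is too low. The completeness check does not help, because it cannot reveal an event nobody was asked about.

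**Working it through.** **No figure to reproduce.** The Protocol article gives no expected event rate, power or error rate for this criterion. It gives only the limit of 1 person, which is 1/30 = 3.3% if all 30 are injected.

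**Inputs from the document**
- Sample: "Thirty adults (over 18 years of age) with post-traumatic GON will be randomized into one of three groups" (abstract, Methods), allocated "in a 1:1 fashion to one of three treatment arms" (Blinding and randomization). So n = 30 in total, about 10 per arm.
- Pass rule: at most 1 person with an adverse event across the whole trial (Primary outcomes).

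**Assumed inputs, not in the document**
- p: true share of injected people with an adverse event.
- s: share of affected people who come to the trial's notice by any route, including the 30-minute window.

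**Formula.** With q = p × s, the chance of meeting the criterion is

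P(X ≤ 1) = (1 − q)^n + n × q × (1 − q)^(n − 1).

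Example, p = 10% and s = 1: 0.90^30 + 30 × 0.10 × 0.90^29 = 0.0424 + 0.1413 = 0.184.

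Example, p = 10% and s = 0.5, so q = 0.05: 0.95^30 + 30 × 0.05 × 0.95^29 = 0.2146 + 0.3389 = 0.554.

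**Results, n = 30**

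| True rate p | s = 1 | s = 0.75 | s = 0.5 | s = 0.25 |
|---|---|---|---|---|
| 5% | 0.554 | 0.689 | 0.828 | 0.946 |
| 10% | 0.184 | 0.331 | 0.554 | 0.828 |
| 20% | 0.011 | 0.048 | 0.184 | 0.554 |
| 30% | <0.001 | 0.005 | 0.048 | 0.331 |

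**What the observation window does.** Suppose half of the affected people are caught in the 30 minutes (an assumption) and a share r of the rest report later. Then s = 0.5 + 0.5 × r.

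| r | s | P at p = 10% | P at p = 20% |
|---|---|---|---|
| 1 | 1 | 0.184 | 0.011 |
| 0.5 | 0.75 | 0.331 | 0.048 |
| 0.25 | 0.625 | 0.433 | 0.096 |
| 0 | 0.5 | 0.554 | 0.184 |

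The window caps the distortion. If half are always seen on site, s cannot fall below 0.5, and at a true rate of 20% the criterion is still failed most of the time.

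**Fewer people injected.** If attendance just met its own 70% mark, n = 0.70 × 30 = 21. For s = 1, 0.75 and 0.5, the chance is then 0.365, 0.526 and 0.717 at p = 10%, and 0.058, 0.155 and 0.365 at p = 20%. The pattern is the same.

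**The case against.** A reader might infer that adverse events reach the trial only if a participant telephones or emails. The document does not support that. Under Interventions, staff watch every participant for 30 minutes for largely the same minor reactions that Primary outcomes lists. Any calculation in which nobody is detected on the day is therefore a worst case. For example, with 3 truly affected people, each noticed with probability 0.3, the chance of counting at most 1 is 0.7^3 + 3 × 0.3 × 0.7^2 = 0.784. If half are caught in the window, detection rises to 0.5 + 0.5 × 0.3 = 0.65 and the chance falls to 0.35^3 + 3 × 0.65 × 0.35^2 = 0.28.

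Three further objections deserve weight:

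- The article condenses a fuller protocol, and adverse-event forms may exist there. The reporting sentence is in the passive, does not name the participant as the one who reports, and does not say that nothing is solicited. However, the article does not leave the matter to another document. It states a route, that route is reactive, and it feeds a primary outcome. That the participant initiates the report is the natural reading of the follow-up contact.
- Neither the event rate nor the reporting rate is known, and that minor events go unreported is general experience and not a figure in the document. This stands. It limits what can be said about size but not about direction.
- Asking about any new symptom over 3 months in people with post-traumatic headache would collect background complaints; Measures already lists nausea and vomiting among the associated headache symptoms. Counted without sorting, these could by themselves exceed a limit of one person. This also stands, and the fix must deal with it.

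**Conclusion.** The concern holds for the period after the 30-minute observation. From then to 3 months the article describes only spontaneous reporting, and a primary criterion that allows one affected person can be met because later minor events were not counted.

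The direction is certain; the size is not. With 30 injected and independent events, dropping from full detection to 50% raises the chance of a pass from 0.18 to 0.55 at a true rate of 10%, and from 0.01 to 0.18 at 20%. Both rates are assumptions. The distortion is small if most events occur and are recorded within the window, and larger if they arise later, as injection-site pain can.

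A reader might also infer that a pass would declare PRP safe. The document does not go that far: the criterion covers all three arms together, and Data analysis calls for descriptive adverse-effect profiles and cautious interpretation of preliminary results. What is at stake is the feasibility decision and the event rate carried into a larger trial. The change is worth making because a primary outcome is affected and the remedy is cheap.

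**What to change.** Under Data management and monitoring, add one adverse-event question, worded identically in all arms, to the existing REDCap questionnaires at 1 week, 1 month and 3 months. Keep telephone and email for urgent events.

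Under Primary outcomes, state that the criterion is judged on three sources together: the 30-minute observations, the solicited answers and the spontaneous reports, with results shown by arm. Count events that are new or worsened since injection, and have their relation to the injection classified by someone blind to arm, so that background headache symptoms do not count against the limit. At the same time, make the abstract and Primary outcomes agree on whether events or people are counted.

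The cost is a slightly longer form, the blinded classification and an ethics amendment. Study status says recruitment was under way, and Protocol amendments gives the route for such a change. Participants who completed follow-up before the change will have been asked less, so events should be reported separately for those before and after it. The recorded count may rise and make the criterion harder to meet.
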